#### Mechanism outcomes

2.4.3

Blood and fecal samples will be collected from all participants at baseline and at the end of the treatment period (week 4). Fasting blood samples (20 mL) will be drawn from the antecubital vein between 7:00 and 9:00 AM. The samples will then be centrifuged at 3,000 rpm for 15 min at 4°C, and the resulting serum will be stored at −80°C. Fecal samples will be collected immediately after morning defecation, placed into sterilized fecal containers, and stored at −80°C. The mechanisms of LSM will be examined through serum biochemical markers, gut microbiota composition, and metabolomic profiling.

Serum biochemical markers will include neurotransmitters, inflammatory cytokines, and endocrine hormones. Neurotransmitters to be measured are 5-hydroxytryptamine (5-HT) and gamma-aminobutyric acid (GABA). Inflammatory markers will cover interleukin-1β (IL-1β), interleukin-6 (IL-6), and tumor necrosis factor-α (TNF-α). Hormonal analysis will focus on melatonin and hormones associated with the hypothalamic-pituitary-adrenal (HPA) axis, such as adrenocorticotropic hormone (ACTH), corticotropin-releasing hormone (CRH), and cortisol (CORT). All measurements will be conducted using enzyme-linked immunosorbent assays (ELISA).

Gut microbiota composition in fecal samples will be analyzed through 16S rRNA gene sequencing. α diversity will be assessed using observed ASV, Shannon, Simpson, and Chao1 indices, while β diversity will be evaluated through principal coordinates analysis (PCoA) based on the Bray–Curtis distance matrix. The linear discriminant analysis effect size (LEfSe) model will be applied to identify differentially abundant taxa between groups.

Metabolomic profiling of serum samples will be performed using non-targeted liquid chromatography-mass spectrometry (LC-MS) (26). Principal component analysis (PCA) and partial least squares discriminant analysis (PLS-DA) will be used to visualize metabolic patterns across groups. Key differential metabolites will be identified based on variable importance in projection (VIP) scores from the PLS-DA model. Additionally, non-targeted quantification of short-chain fatty acids (SCFAs) in fecal samples will be conducted via gas chromatography-mass spectrometry (GC-MS) (27).

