### Statistical analysis

2.9

The analysis will be conducted based on the intent-to-treat (ITT) population, defined as participants who complete baseline assessments and have at least one follow-up measurement. The Shapiro–Wilk test will be employed to assess the normality of the data distribution. For continuously measured repeated data, such as ISI scores, PSQI scores, PFS scores, FACT-B scores, and hypnotic medication dosages, a mixed-effects model adjusted for baseline values will be used to compare longitudinal changes from baseline across follow-up time points between groups. The model will include fixed effects for endocrine therapy status (yes or no), time, group, and the interaction between time and group, while treating individual participants as random effects. Given that mixed-effects models can accommodate participants with at least one outcome measurement, no imputation will be performed for missing values in the primary analysis (30).

For non-repeated continuous variables, such as serum biochemical markers and gut microbiota abundance, between-group comparisons will be performed using either the *t*-test or Mann–Whitney *U* test, depending on data distribution. Categorical variables, including treatment response rates and incidence of adverse events, will be analyzed using chi-square or Fisher’s exact tests. Correlation analyses between ISI scores, differential serum biochemical markers, differential metabolites, and key gut microbiota will be performed using Pearson or Spearman correlation coefficients. Missing values for data analyzed using non-mixed effect models will be managed using multiple imputation methods.

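### Multiple imputation is prescribed for all data outside the mixed models, including the microbiota and metabolomic analyses, whose outputs cannot be pooled and whose absent profiles cannot sensibly be drawn

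*Protocol article*

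**What the plan says.** The Statistical analysis section of the protocol article has two missing-data rules.

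- For outcomes analysed by mixed models (ISI, PSQI, PFS, FACT-B, hypnotic dose): "no imputation will be performed for missing values in the primary analysis".
- For everything else: "Missing values for data analyzed using non-mixed effect models will be managed using multiple imputation methods". No exception is given.

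The paragraph that holds the second rule names these analyses:

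- Serum markers and the abundance of gut taxa are tested as follows: "between-group comparisons will be performed using either the *t*-test or Mann–Whitney *U* test, depending on data distribution".
- Treatment response and harms are taken as categorical, and the plan is that they "will be analyzed using chi-square or Fisher’s exact tests".
- Correlations of ISI with markers, metabolites and key taxa "will be performed using Pearson or Spearman correlation coefficients".

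The Mechanism outcomes section adds further analyses that are not mixed models. For stool: "The linear discriminant analysis effect size (LEfSe) model will be applied to identify differentially abundant taxa between groups". For serum metabolomics, PCA and PLS-DA are planned, and "Key differential metabolites will be identified based on variable importance in projection (VIP) scores from the PLS-DA model". Blood and stool are taken twice, at baseline and at week 4.

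**The concern.** Multiple imputation has two steps: fill in the missing values several times from a credible model, then combine the results. Combining by Rubin's rules needs an estimate and its standard error from each completed data set. For the omics part of this plan, both steps are in difficulty.

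At stake are the lists of key taxa and metabolites, and the correlations built on them. If the rule is followed, profiles generated by a model enter the search for features that separate the arms. The Discussion presents the multi-omics work as a main feature of the trial, so its missing-data rule should be one that can be carried out.

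A smaller issue concerns treatment response, a secondary outcome. The named test for it yields a p-value, and a p-value as such cannot be averaged over imputations. The stated test and the stated missing-data rule have to be reconciled there.

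**Working it through.** **1. The plan's own figure.** The only calculated design figure is the sample size.

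- Inputs (Sample size section): pilot changes 6.82 (SD 4.06) and 3.24 (SD 2.38), two-sided alpha 0.05, power 0.90, dropout 10%.
- Difference 6.82 − 3.24 = 3.58. Pooled SD √[(4.06² + 2.38²)/2] = 3.33. d = 3.58/3.33 = 1.08, as stated.
- With unequal variances, power is 0.893 at 19 per group and 0.909 at 20, so n = 20.
- 20/0.9 = 22.2, rounded up to 23. Two endocrine strata give 2 × 23 = 46, as stated, and the plan then rounds to 50.

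The figure reproduces. Only the 50 per arm and the 10% are carried forward.

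**2. How many profiles the rule could require.** 10% of 50 is 5 per arm. The analysis population needs a baseline and at least one follow-up measurement, and the first follow-up is at week 2.

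| When the participant drops out | In the analysis set? | Week-4 sample to impute? |
|---|---|---|
| Before any follow-up | No | No |
| After a first follow-up, before week 4 | Yes | Yes |
| After week 4 | Yes | No, sample already taken |

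Dropout therefore produces between 0 and about 5 absent week-4 profiles per arm. The upper end needs all of it to fall in the middle row. Samples lost for other reasons would add to this, and the article gives no rate for them.

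**3. Can an absent profile be drawn?** The article gives no feature counts. I assume that 16S sequencing and non-targeted LC-MS give far more features than the trial has participants. With 90 complete participants, the sample covariance matrix of the features has rank at most 90 − 1 = 89. A joint imputation model for more features than that is not identified by the data without strong added structure. There is also a circularity. If arm is in the imputation model, drawn profiles carry the fitted arm difference into LEfSe and PLS-DA, which then look for arm differences. If arm is left out, the draws dilute any difference.

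**4. Can the results be pooled?**

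| Planned analysis | Output | Quantity for Rubin's rules |
|---|---|---|
| LEfSe | Selected taxa | None as a single estimate with standard error |
| PCA, PCoA | Ordination | None |
| PLS-DA with VIP | Ranking of metabolites | None |
| t-test | Mean difference | Yes |
| Mann–Whitney | p-value | Yes, through P(X>Y) |
| Chi-square, Fisher | p-value | Yes, through a risk difference or log odds ratio |
| Correlations | Coefficient | Yes, through Fisher z |

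**5. Check on the lower half of that table.** Simulation with 50 per arm, 10% missing completely at random, 20 imputations from baseline and arm, and 1,500 replicates. Assumptions not in the article: normal outcome on the analysis scale, baseline correlation 0.5, and missingness set equal to the dropout allowance.

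| Analysis | Rejections under the null | Rejections at a 0.5 SD shift |
|---|---|---|
| Pooled P(X>Y) after imputation | 5.3% | 66% |
| Pooled risk difference after imputation | 3.6% | 49% |
| Mann–Whitney, complete cases | 5.7% | 64% |

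The simulation standard error at 5% is √(0.05 × 0.95/1500) = 0.56 percentage points. The two rank-based results agree with 5%, and the risk difference is somewhat conservative. The rule is workable for these outcomes once an estimate is chosen.

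**The case against.** The strongest reply is that imputation models and pooling quantities are usually left to the full protocol or analysis plan, which are not shown. An article that says only multiple imputation has made no error by omitting them. That stands, and I make no point of the missing detail. It does not rescue the omics analyses, because the sentence sets a rule without exception and microbiota abundance is named in the same paragraph. A later document could exempt these data only by departing from that sentence.

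A second reply is that these analyses are mechanistic and that the primary ISI analysis needs no imputation. That also stands, and it limits the weight of the point. Multiple imputation of ISI as a sensitivity analysis is not in question either.

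Three stronger readings are tempting, and the document does not support them.

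- A reader might infer that rank and exact tests leave nothing to pool, so that responder results would be invalid. Steps 4 and 5 of the working show otherwise. Only the bare p-value is unusable.
- A reader might infer that assay values below a detection limit would be imputed as if they were ordinary missing values, weakening marker effects. The article plans ELISA but nowhere mentions detection limits or codes non-detects as missing, so there is nothing to criticise.
- A reader might infer that 5 of 50 profiles per arm will be generated. That is the upper end for dropout and not an expected value.

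**Conclusion.** The point holds in a limited form. As written, the rule covers LEfSe, PCA and PLS-DA/VIP, whose outputs cannot be combined by Rubin's rules, and it asks for entire absent week-4 profiles to be drawn from about 50 participants per arm. Through dropout this concerns 0 to about 5 profiles per arm. The conclusion rests on a literal reading of an unqualified sentence, and on the assumption that features far outnumber participants.

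For treatment response, serum markers and correlations, multiple imputation is feasible, provided that an estimate is pooled instead of a p-value. This is a modest correction to secondary and mechanistic analyses.

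**What to change.** Replace the unqualified sentence with a short paragraph that says:

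1. Multiple imputation is limited to outcomes with a poolable estimate.
2. For treatment response, ISI is imputed, response is derived in each completed data set, and a risk difference or log odds ratio is pooled. This takes the place of a chi-square or Fisher p-value.
3. Microbiota, metabolome and short-chain fatty acids are analysed on available samples. Absent samples are not imputed, and the number missing is reported by arm.
4. Week-4 serum markers are compared with the baseline value in the model. The baseline sample is already collected, and the adjusted mean difference can be pooled if imputation is used.

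The cost is a paragraph of wording and no new data. The small downside is that omics analyses use only participants with samples. Little is lost by that, since a drawn profile adds no measured information.

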### Study design

2.1

This study is designed as a single-center, rater-masked, parallel-arm, randomized controlled trial. We will recruit 100 breast cancer survivors diagnosed with insomnia from the Hospital of Chengdu University of Traditional Chinese Medicine. Participants will be randomly allocated in a 1:1 ratio to either the LSM intervention group or the waitlist control (WC) group. The study will span 9 weeks, comprising a 1-week baseline assessment phase, a 4-week intervention phase, and a 4-week post-treatment follow-up phase. Throughout the 4-week treatment period, both groups will receive standard care, with the LSM group additionally undergoing LSM therapy twice per week. This trial has been rigorously designed according to the Consolidated Standards of Reporting Trials (CONSORT) guidelines and will be reported following the 2013 Standard Protocol Items: Recommendations for Interventional Trials (SPIRIT) Checklist (see Supplementary material S1). The study flow is depicted in Figure 1.

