#### Primary efficacy outcome

2.4.1

The primary efficacy outcome will be the change in ISI score from baseline to the end of the 4-week treatment period. The ISI is a validated 7-item self-report measure that has demonstrated strong internal consistency and construct validity for evaluating insomnia severity in cancer patients (20). ISI scores are categorized as follows: 0–7 (no clinically significant insomnia), 8–14 (mild insomnia), 15–21 (moderate insomnia), and 22–28 (severe insomnia) (21). ISI assessments will be conducted at baseline, as well as at weeks 2, 4, 6, and 8 following the start of treatment.

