For the primary efficacy outcome (the change in the ISI score from baseline to the end of the 4-week treatment period), subgroup analyses will be conducted based on hypnotic medication use (yes, no) and insomnia severity (mild, moderate, severe) to further explore potential variations in the treatment effects of LSM across different subgroups. Additionally, sensitivity analyses will be performed for the primary efficacy outcome. Specifically, if missing values or non-normally distributed data are present, multiple imputation methods will be used to assess the impact of missing data, and generalized estimating equations will be employed as a non-parametric alternative for non-normally distributed data. Pre-specified per-protocol analyses will also be conducted. The per-protocol set will include all participants who completed the intervention and follow-up according to the study protocol. The results of the primary analysis will be compared with those from these sensitivity analyses to assess robustness.

All statistical analyses will be carried out using SPSS (version 26.0) and R (version 4.3.1). Two-tailed significance testing will be applied, with a *p*-value threshold of ≤ 0.05 indicating statistical significance.

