In summary, this study employs a multidisciplinary approach to explore the potential effects of LSM on biological systems associated with insomnia in breast cancer survivors, aiming to build a strong evidence base. The findings are expected to provide valuable insights for clinical practice and validate the potential of LSM as an effective non-pharmacological treatment for insomnia. By addressing challenges related to the significant side effects of pharmacotherapy and the limited accessibility of cognitive behavioral therapy, LSM may offer a more effective and accessible alternative. However, several limitations must be acknowledged. First, as a single-center trial, the generalizability of the findings may be limited, and future multi-center studies will help confirm these results in a more diverse patient population. Second, due to the current lack of a well-established LSM placebo tool, this study adopted an open-label design. The absence of blinding may introduce bias, particularly in subjective outcome measures, where participants’ expectations could influence their reported outcomes, potentially compromising the accuracy of the results. Future studies should focus on developing an appropriate placebo tool for LSM and employ a double-blind trial design to more objectively assess its efficacy. Lastly, the relatively short follow-up period of 4 weeks limits our ability to evaluate the long-term effects and sustainability of the treatment. Longer follow-up periods are recommended in future research to assess the durability of the treatment benefits.

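### The per-protocol check on the week-4 ISI result also requires completed follow-up after treatment, so it mixes treatment adherence with post-endpoint retention

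*Protocol article*

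**What the plan says.** The endpoint is fixed in section 2.4.1: "The primary efficacy outcome will be the change in ISI score from baseline to the end of the 4-week treatment period". The same section gives the measurement times: "ISI assessments will be conducted at baseline, as well as at weeks 2, 4, 6, and 8 following the start of treatment". Two of the four post-baseline ISI assessments therefore come after the primary endpoint.

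Section 2.1 divides the study into "a 1-week baseline assessment phase, a 4-week intervention phase, and a 4-week post-treatment follow-up phase". The Discussion uses the term in the same sense when it lists as a limitation that "the relatively short follow-up period of 4 weeks limits our ability to evaluate the long-term effects".

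Section 2.9 introduces the checks on the primary result: "Additionally, sensitivity analyses will be performed for the primary efficacy outcome". These include multiple imputation, generalized estimating equations and a per-protocol analysis. The population for the last is defined as follows: "The per-protocol set will include all participants who completed the intervention and follow-up according to the study protocol". Their purpose is then stated: "The results of the primary analysis will be compared with those from these sensitivity analyses to assess robustness".

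The primary analysis has no such restriction. It is a mixed-effects model on everyone with a baseline assessment and at least one later measurement.

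**The concern.** A per-protocol analysis of a week-4 outcome should ask what the effect looks like among participants who followed the protocol up to week 4. The stated set asks more. Completing follow-up can only be judged after the outcome has been measured, so a valid week-4 ISI can be discarded because of something that happened later.

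That matters because week-4 improvement comes before attendance at weeks 6 and 8 and could influence it. The trial is open-label, the ISI is self-reported, and participants in the treated and waitlist arms have different reasons to keep attending. Retention after week 4 may therefore depend on response, and differently by arm.

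What is at stake is how the robustness comparison is read. If the per-protocol and intention-to-treat estimates differ, the reader cannot tell how much comes from adherence to treatment and how much from who stayed in follow-up.

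**Working it through.** **1. Reading the passages together.** Section 2.9 names two things to complete, the intervention and follow-up, and section 2.1 names two matching phases, each of 4 weeks. Section 2.9 also uses follow-up more loosely, for any measurement after baseline. In that sense, completing follow-up still includes weeks 6 and 8. No statement ends follow-up at week 4. On either reading, the set for the week-4 check depends on what happens after week 4.

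**2. The plan's own figures (section 2.8).**
- Pilot ISI reductions: 6.82 (SD 4.06) with LSM and 3.24 (SD 2.38) on the waitlist; difference 6.82 − 3.24 = 3.58.
- Cohen's d = 3.58 / √[(4.06² + 2.38²)/2] = 3.58 / 3.328 = 1.076, which agrees with the stated 1.08.
- Unequal-variance t-test, two-sided 0.05: power is 0.893 at 19 per group and 0.909 at 20, so 20 per group are needed for 0.90.
- With 10% dropout: 20 / 0.90 = 22.2, rounded up to 23. Two strata × 23 = 46 per group, the stated figure, before rounding to 50.

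**3. How many are affected.** The document gives 10% dropout but not when it occurs. Assume that half falls after week 4.
- 10% of 100 = 10 losses, of which 5 are late. The set as written keeps at most 45 of 50 per group; a set running through week 4 keeps about 47.5.
- With 20% dropout and the same split, the figures are 40 and 45.
- Power under the pilot inputs is 0.9989 at 45 per group and 0.9973 at 40. Power is not the issue.

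**4. How far an arm mean could move.** Let a fraction q of an arm be lost late, with a mean change δ points worse than the arm mean m. The retained mean is [m − q(m − δ)] / (1 − q) = m + qδ/(1 − q). With q = 0.10 and δ = 3 (both assumptions):
- Shift = 0.10 × 3 / 0.90 = 0.33 points; 0.33 / 3.58 = 9%.
- Loss in the LSM arm only: difference 3.58 + 0.33 = 3.91.
- Loss in the waitlist arm only: difference 3.58 − 0.33 = 3.25.
- Equal loss with equal δ in both arms: the shifts cancel.

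For scale, the standard error of the difference at 45 per arm is √[(4.06² + 2.38²)/45] = √(22.15/45) = 0.70, so 0.33 is just under half a standard error. These are shifts in raw means; a baseline-adjusted mixed model could give somewhat different values.

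**5. Range under other assumptions.** The table shows simulated differences for normal data with the pilot mean and SD, and late loss in the LSM arm only.

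| Late loss in LSM arm | Loss odds double per SD of poorer change | All the worst responders leave |
|---|---|---|
| 5% | 3.72 | 4.02 |
| 10% | 3.85 | 4.37 |
| 20% | 4.10 | 5.00 |

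The last column is an extreme bound, not an expectation.

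**The case against.** Four counter-arguments deserve weight.

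*The exclusion rule is partly inferred.* A reader might conclude that one missed visit at week 6 or 8 removes a participant. The article does not say so. Completed could mean only that she did not withdraw before the end, and visit-level criteria are commonly left to an analysis plan. This stands, and the point is limited accordingly to participants who did not complete follow-up. It does not remove the problem, because the requirement to complete follow-up is stated, not omitted.

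*The set suits the model.* The week-4 contrast comes from one longitudinal model that also uses weeks 2, 6 and 8, and a set of full completers is a conventional population for it. That is fair. But a mixed model does not need complete schedules, as section 2.9 itself notes when it declines to impute, so the model gives no reason to drop these participants from a week-4 check.

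*Every per-protocol set selects on post-randomisation behaviour.* A reader might infer that the planned comparison tells us nothing about robustness. That goes too far. Agreement between the intention-to-treat result and a stricter completer set is still informative, and a set defined through week 4 would also be selected on adherence and on having a week-4 ISI. The extra requirement adds one avoidable layer of selection; it blurs the check without making it unreadable.

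*The size is small and the assumptions are stacked.* This also stands. The 0.33-point example needs all five assumed late losses to fall in one arm.

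**Conclusion.** The point holds as a minor flaw in a stated definition. The per-protocol set offered as a check on a week-4 outcome requires completion of a phase that begins after that outcome is measured, so the comparison with the primary result mixes adherence with post-endpoint retention.

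It would be wrong to infer that the primary result is biased or underpowered. The intention-to-treat mixed model keeps participants who do not complete follow-up, multiple imputation is planned as a separate check on missing data, and power under the pilot inputs stays above 0.99 at 40 to 45 per group.

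The direction of any bias depends on which arm loses whom, and the document gives no loss rate after week 4. A shift of 0.33 points, 9% of the pilot difference and under half a standard error, illustrates a one-sided loss of 10% with a mean change 3 points worse than the arm mean. Similar loss in both arms would give little or no shift. The effect is probably small, but it can be avoided at almost no cost.

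**What to change.** In section 2.9, define the per-protocol set for the primary outcome as participants whose conduct conformed to the protocol through week 4 and who have a week-4 ISI, regardless of attendance at weeks 6 and 8. Require completed follow-up only for per-protocol analyses of the week-6 and week-8 outcomes, and state what counts as completed. Add that the per-protocol result still conditions on post-randomisation behaviour and is supportive only.

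This takes two or three sentences. It needs no new data, visits or staff and leaves the sample size unchanged. It should be settled before the analysis begins.
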